### Follow-up

2.8

Patients will be followed up 6 months after the end of treatment. The outcomes scales will be assessed to evaluate the long-term efficacy of acupuncture.

### Data management and quality control

2.9

To ensure trial consistency and accuracy, all team members will receive standardized training prior to study initiation. All members will receive training on the localization of acupoints, the application of sham needles, the evaluation of assessment scales, patient communication, as well as the methods and time points for follow-up. The researcher responsible for the assessment needs to be proficient in the questions and operations in the case report form (CRF), conduct an objective assessment of the subjects, and both the assessor and the subjects need to sign the CRF to ensure the reliability and integrity of the data. Researchers will strictly keep the case observation forms and set access permissions for electronic data, allowing only authorized personnel to enter, modify and view the data to ensure data security and protect the privacy of the subjects. Data quality will be monitored regularly to check whether the data are missing, wrong or invalid, and to ensure the completeness and rationality of the data.

### Statistical analysis

2.10

In this study, IBM SPSS Statistics 26.0 statistical software will be used to analyze the collected clinical data. Shapiro–Wilk will be used to test the normality before statistical analysis. Counting data is expressed as a percentage using a chi-square test. The measurement data meeting the normal distribution will be represented by mean ± standard deviation, while those not meeting the normal distribution will be represented by quartile. The independent sample t test will be used to compare the two groups with normal distribution and homogeneous variance, and the Mann–Whitney U test will be used to compare the two groups with non-normal distribution. The comparison difference before and after treatment will be treated by paired sample t test with normal distribution, and Wilcoxon rank sum test with abnormal distribution. The two groups of repeated measurement data do not meet the normal distribution of the generalized estimation equation, the simple effect in the group will be analyzed by Friedman test. Two-sided test will be applied uniformly in this study, and *p* ≤ 0.05 will be the standard of statistical significance.

To evaluate the clinical relevance of the findings, we will perform a responder analysis based on the minimal clinically important difference (MCID) for the MoCA. Based on previous literature in cognitive impairment (21), a change of ≥1.22 points on the MoCA scale will be considered clinically meaningful. Participants who show an improvement of ≥1.22 points from baseline to post-treatment will be classified as ‘responders’. The difference in the proportion of responders between the study groups will be compared using a Chi-square test, with a *p*-value < 0.05 considered statistically significant.

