#### Inclusion criteria

2.1.1

Meet the diagnostic criteria for idiopathic PD and PD-MCI.Meet the diagnostic criteria of TCM tremor syndrome and stupidness.Patients aged 50–70 years.MoCA scale score range of 18 to 25.MMSE scale score range of 21 to 26.Hoehn-Yahr staging scale staged 1–3.Do not participate in other drugs, acupuncture and other treatments or clinical trials within 1 month.Voluntarily join the study and sign the informed consent.

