### Sample size

2.2

Aligned with the study’s objective, Montreal Cognitive Assessment Scale (MoCA) was chosen as the primary outcome. According to the results of previous experiments and literature review (13, 14), the mean and standard deviation of MoCA scale in PD-MCI patients received acupuncture combined with anti-PD drug treatment were 25.32 and 4.34, while there were 21.48 and 4.44, respectively, in PD-MCI patients who received sham acupuncture combined with anti-PD drug treatment. PASS V.15.0 (NCSS, Kaysville, UT, United States) was used to calculate the sample size. We set 90% for power level and 5% for two-sided significance level. It was estimated that there were about 29 patients in each group, and considering the dropout rate of 20%, the total sample size needed for study is 72, with 36 patients in each group.

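### Section 2.10 fixes no single primary MoCA test: it pairs an unadjusted t test or Mann–Whitney U with a normality pre-test, where one baseline-adjusted ANCOVA would be more precise at no cost

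*Protocol article*

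**What the plan says.** Section 2.2 (Sample size) states that "Montreal Cognitive Assessment Scale (MoCA) was chosen as the primary outcome". It sizes the trial on score levels: patients who "received acupuncture combined with anti-PD drug treatment were 25.32 and 4.34", "while there were 21.48 and 4.44, respectively, in PD-MCI patients who received sham acupuncture". The outcome schedule (Table 2) has MoCA at weeks 0, 5 and 25, and section 2.1.1 makes "MoCA scale score range of 18 to 25" an entry criterion, so every randomised patient has a baseline value.

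Section 2.10 (Statistical analysis) says that Shapiro–Wilk "will be used to test the normality before statistical analysis". Then: "The independent sample t test will be used to compare the two groups with normal distribution and homogeneous variance", with Mann–Whitney U for non-normal data. No covariate is named, and the section does not say whether these tests take the week-5 score or the change from baseline.

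Baseline does appear elsewhere in section 2.10, in three places:
- before/after comparisons (paired t or Wilcoxon);
- one unclear sentence that mentions a generalised estimating equation and a Friedman test for non-normal repeated measurements;
- a responder analysis on improvement of at least 1.22 MoCA points.

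None of these is a stated baseline-adjusted comparison of mean MoCA between the groups.

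**The concern.** Two separate matters are involved.

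**Precision.** A baseline measure of the same scale normally predicts the later score. A between-group test that leaves it out carries variance that could be removed. Randomisation is simple (section 2.3), so nothing in the design limits a chance difference in baseline MoCA between two arms of 36.

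**Pre-specification.** The t test targets a mean difference and Mann–Whitney U a rank comparison. If a preliminary test on the outcome data chooses between them, the primary test and the quantity estimated are unknown until the data are seen. The rule also has gaps. Normal data with unequal variances have no assigned test, and the text does not say what happens when one arm passes the normality test and the other fails. MoCA is a whole-point scale with a maximum of 30, so the second case could easily arise.

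**Working it through.** **Inputs from section 2.2.** Means 25.32 and 21.48, SDs 4.34 and 4.44, two-sided 5%, 90% power ("We set 90% for power level and 5% for two-sided significance level"), 29 evaluable per arm.

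- Difference: 25.32 − 21.48 = 3.84.
- Pooled SD: √[(4.34² + 4.44²)/2] = 4.39.
- Standardised difference: 3.84/4.39 = 0.875.

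**Reproducing the plan's figure.** The noncentral-t calculation for an unadjusted two-sample t test gives 28.46, so 29 per arm, which agrees with "It was estimated that there were about 29 patients in each group". Power at 29 per arm is 90.5%. The trial is therefore sized without use of baseline.

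**Correlation r between baseline and week 5.** The document gives none, so it is an assumption. The entry range bounds it informally. If baseline scores were spread evenly over the eight values 18 to 25, their SD would be √[(8² − 1)/12] = 2.29. With a week-5 SD of 4.39 and a regression slope of 1, r = 2.29/4.39 = 0.52. I use 0.3 to 0.5.

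**Gain from ANCOVA.** Residual SD = 4.39 × √(1 − r²), put into the same noncentral-t power at 29 per arm (the one degree of freedom spent on the covariate is ignored):

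| r | Residual SD | Variance removed | Power at 3.84 points | Power at 2 points |
|---|---|---|---|---|
| unadjusted | 4.39 | – | 90.5% | 39.9% |
| 0.3 | 4.19 | 9% | 92.9% | 43.2% |
| 0.5 | 3.80 | 25% | 96.6% | 50.4% |

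The 2-point case is illustrative; the document does not assume it.

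**Chance baseline imbalance.** With baseline SD 2.29 (assumed as above) and 36 per arm, the 95% range of the baseline difference is ±1.96 × 2.29 × √(2/36) = ±1.06 points. The slope is r × 4.39/2.29, that is 0.58 at r = 0.3 and 0.96 at r = 0.5. The part carried into the week-5 contrast is then about ±0.6 to ±1.0 points. The unadjusted standard error already allows for this on average; ANCOVA takes it out of the estimate.

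**The pre-test.** Simulated with normal scores, SD 4.39, rounded and capped at 30, 29 per arm, 6,000 runs per scenario:

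- Type I error of the pre-test rule was 4.6% to 5.1%.
- Power of the rule was within 0.4 percentage points of the plain t test.
- In a separate run of 10,000 trials with no true difference, t and Mann–Whitney disagreed on significance in 1.6%.
- Shapiro–Wilk rejected in at least one arm in about 12% of trials with no difference, 27% at 2.5 points and 57% to 58% at 3.84 points. The likely choice of test thus depends on the treatment effect itself, because a higher mean pushes scores against the ceiling.

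In a further 4,000 runs with the plan's arm-specific means and SDs, Shapiro–Wilk rejected in about 54% of acupuncture arms and 6% of sham arms, and the arms disagreed in about 53% of trials.

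**The case against.** The strongest reply is that an unadjusted t test in a randomised trial is valid and that this one meets its 90% target under the stated assumptions. That stands. A reader might infer that the trial is underpowered or its primary test wrong; the recalculation does not support either.

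A reader might also expect large gains, such as those at r = 0.7 (67% power at 2 points). The entry range of 18 to 25 makes this hard to reach. With an evenly spread baseline it needs a slope of 0.7 × 4.39/2.29 = 1.34, so I do not rely on it.

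A third tempting inference is that the pre-test itself wastes power or inflates type I error. The simulation shows almost no effect on either.

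Nor is baseline wholly ignored. The responder analysis uses change, and a group-by-time generalised estimating equation over weeks 0, 5 and 25 would use baseline if that is what the unclear sentence means. But the sentence names no model terms and is tied to non-normal data, and the responder analysis is supplementary. The t test might also be meant for change scores; the text leaves this open, and the sizing on score levels points the other way.

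The simulated 53% depends on shape. Capping at 30 puts about 17% of acupuncture patients at exactly 30 and lowers that arm's mean and SD to about 25.0 and 3.83, so the simulated arm no longer has the quoted moments. The figure shows that the unassigned case is plausible; it is not a forecast. The gap for unequal variances is minor, since the planning SDs are 4.34 and 4.44.

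Finally, a separate analysis plan might name an ANCOVA. The protocol itself states the rule, however, so such a plan would have to depart from section 2.10.

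**Conclusion.** The point holds as an efficiency and pre-specification matter, and its label is free improvement. Baseline adjustment would add about 2 to 6 percentage points of power at the planned 3.84-point difference (from 90.5% to 93%–97%) and about 3 to 10 points if the true difference were 2 (from 40% to 43%–50%). Both ranges rest on an assumed correlation of 0.3 to 0.5, an SD of 4.39 and 29 evaluable patients per arm. The gain matters most if the true effect is smaller than planned.

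The fault of the pre-test is that the primary test, and whether it estimates a mean difference or compares ranks, is left to the data, with incomplete branching. The document does not support a claim of invalid inference, material error inflation or failure to reach the planned power.

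**What to change.** In section 2.10, replace the branching rule for the primary outcome with one named analysis: an ANCOVA of week-5 MoCA on treatment group with baseline MoCA as covariate, reporting the adjusted mean difference and its 95% confidence interval, not conditional on any normality test. Make rank-based or robust analyses sensitivity analyses. Reword the sentence on generalised estimating equations and the Friedman test so that its role is clear and does not compete with the primary analysis. The same baseline adjustment can be used for MMSE and UPDRS III.

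The change should be made before unblinding. It costs one paragraph of wording and needs no extra patients, visits or data. The sample size can stay as it is, since the present calculation is conservative for the adjusted analysis.

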This randomized controlled trial is designed based on previous acupuncture research. It aims to evaluate the cognitive function improvement in PD-MCI patients receiving either verum or placebo acupuncture. In this study, we focus on the clinical efficacy of acupuncture for PD-MCI in order to provide an evidence-based assessment of acupuncture’s therapeutic value. We hope that we can expand the clinical treatment option for PD-MCI through the study, help to delay the disease progression, and enhance the quality of life of PD patients.

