##### Blood serum index

2.6.2.3

Cognitive impairment in PD is associated with dysfunction of a variety of neurotransmitter systems, including acetylcholinergic, dopaminergic, norepinephrine and 5-hydroxytryptaminergic. When the axons of nerve cells are damaged, they release serum neurofilament light polypeptide (NfL) into the cerebrospinal fluid and eventually into the blood (18). Serum glial cell-derived neurotrophic factor (GDNF) promotes the survival of dopaminergic (DA) neurons in the substantia nigra. GDNF may act in combination with neurotransmitters (HVA, 5-HT, GABA and Ach) to affect attention, memory and executive function in PD-MCI patients (19). Therefore, NfL and GDNF levels can reflect the activity of brain neurons, and NfL and GDNF can be used as biomarkers related to cognitive function.

Serum concentrations of NfL and GDNF will be measured before and at the end of treatment using enzyme-linked immunosorbent assay (ELISA), which follows the kit instructions strictly. Both ELISA kits will be provided by Jiangsu Enzyme Free Industrial Co., LTD.

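### Before/after change in the continuous outcomes is tested within each arm at the same significance standard as the between-arm tests, and no between-arm test of that change is stated

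*Protocol article*

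**What the plan says.** Section 2.10 of the protocol article sets out these tests for continuous outcomes (MoCA, MMSE, UPDRSIII, NfL, GDNF):

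- **Between arms.** "The independent sample t test will be used to compare the two groups with normal distribution and homogeneous variance"; otherwise "the Mann–Whitney U test will be used to compare the two groups with non-normal distribution". Neither clause says whether the week-5 score or the change is compared, or at which visit.
- **Before versus after.** "The comparison difference before and after treatment will be treated by paired sample t test with normal distribution". The non-normal alternative is called a Wilcoxon rank sum test. As the counterpart of a paired t test, it is read here as the paired (signed-rank) version.
- **Repeated measurements.** A sentence that is hard to parse names generalized estimating equations and then adds that "the simple effect in the group will be analyzed by Friedman test". It states no group-by-time contrast.
- **Standard.** "Two-sided test will be applied uniformly in this study", with p ≤ 0.05 as the threshold throughout.

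The same section also defines MoCA responders as those gaining at least 1.22 points from baseline to post-treatment, and compares the proportions between arms by chi-square. Section 2.2 sizes the trial on a between-arm difference in MoCA means. Table 2 schedules MoCA, MMSE and UPDRSIII at weeks 0, 5 and 25. For the biomarkers, "Serum concentrations of NfL and GDNF will be measured before and at the end of treatment".

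**The concern.** The sham arm is there so that whatever both arms share can be subtracted. A paired test in the acupuncture arm does not subtract it. A significant before/after MoCA result mixes any needling effect with familiarity from a repeated test, placebo response over 20 sessions, and any anti-Parkinson drug change, which sections 2.5.1 and 2.5.2 allow and record.

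For all five continuous outcomes, the only significance test that the text expressly attaches to the before/after difference is this within-arm one. For MMSE, UPDRSIII, NfL and GDNF there is not even a responder comparison beside it. Because within-arm and between-arm tests share one threshold and no order of precedence, a report could follow the plan and still state that MoCA improved significantly with acupuncture, or that it improved significantly with acupuncture but not with sham. Neither statement has a 5% error rate for the question of acupuncture against sham.

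**Working it through.** **1. The plan's own sample size (section 2.2).** MoCA means are 25.32 and 21.48, SDs 4.34 and 4.44, power 90%, two-sided alpha 5%.

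- Difference: 25.32 − 21.48 = 3.84.
- Pooled SD: √((4.34² + 4.44²)/2) = 4.39.
- Exact two-sample t power: 0.895 at 28 per arm and 0.905 at 29 per arm.

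The stated figure of about 29 per group reproduces. It is a between-arm calculation, so the trial was designed around the between-arm question.

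**2. How often the within-arm test is significant when acupuncture does nothing.** The document gives neither a non-specific gain nor an SD of change. Both are assumptions here:

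- gain m = 1 MoCA point, equal in both arms;
- SD of change s from 2.5 to 4.4. As a guide, s = SD × √(2(1 − r)) with a score SD of about 4.4 gives 2.49 at retest correlation r = 0.84, 2.78 at r = 0.8, 3.40 at r = 0.7 and 4.39 at r = 0.5.

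The paired t statistic is noncentral t with n − 1 degrees of freedom and noncentrality λ = m√n / s. For n = 29 and s = 2.5, λ = 5.385/2.5 = 2.15; for s = 4.39, λ = 5.385/4.39 = 1.23. With independent arms, the probability that acupuncture is significant and sham is not is (probability of significant improvement in one arm) × (1 − probability of significance in the other). For n = 29 and s = 2.5 this is 0.548 × 0.452 = 0.248.

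| SD of change | n per arm | Acupuncture-arm paired test significant | Acupuncture significant, sham not |
|---|---|---|---|
| 2.5 | 29 | 0.548 | 0.248 |
| 2.78 | 29 | 0.465 | 0.249 |
| 3.40 | 29 | 0.334 | 0.222 |
| 4.39 | 29 | 0.220 | 0.171 |
| 2.5 | 36 | 0.646 | 0.229 |
| 4.39 | 36 | 0.265 | 0.194 |

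Checks: with zero gain the paired test returns 0.05, as it should. The product p(1 − p) cannot exceed 0.25, so about 25% is the ceiling for the discordant pattern. A two-sided 5% between-arm test falsely favours acupuncture with probability 0.025 in every row.

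**3. Sensitivity to the gain** (29 per arm, s from 4.39 down to 2.78): a 0.5-point gain gives 0.09 to 0.16, 1 point gives 0.22 to 0.47, and 1.5 points gives 0.43 to 0.80.

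**4. Is the sample size enough for the between-arm replacement?** For a 3.84-point difference at 90% power (normal approximation, r assumed):

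| r | Change-score t test, n per arm | Baseline-adjusted, n per arm |
|---|---|---|
| 0.5 | 28 | 21 |
| 0.6 | 22 | 18 |
| 0.7 | 17 | 15 |
| 0.8 | 11 | 10 |

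At r = 0.5 the SD of change equals the score SD, so the exact calculation gives 29, as in step 1. The planned 29 evaluable per arm covers every row.

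**The case against.** The strongest reply is that the plan already answers the right question. A t or Mann–Whitney test of week-5 scores between randomized arms holds its 5% error rate and removes equal practice and placebo gains in expectation. Testing change instead of the final score affects precision, not validity. This stands. The defect is not the absence of any valid test but the equal footing given to an invalid one, together with a between-arm test whose variable and visit are left open.

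Three stronger readings are tempting, and the article does not support them.

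- **That change is tested only within arms.** The responder chi-square compares dichotomised MoCA change between arms, and the unnamed variable in the t or Mann–Whitney test might be change.
- **That within-arm results would be reported as an acupuncture effect.** No sentence ties the efficacy conclusion to the paired test; the article only fails to rule this out.
- **That the aim is itself within-arm.** The Introduction says "It aims to evaluate the cognitive function improvement in PD-MCI patients receiving either verum or placebo acupuncture", but this follows directly on a description of a randomized controlled trial and reads naturally as a two-arm comparison.

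It is also fair to say that the before/after test spans two visits; the three-visit data fall under the repeated-measures sentence. The illustration's gain and SD of change are not in the document. In addition, entry is limited to MoCA 18 to 25, so the baseline SD cannot much exceed half the range, (25 − 18)/2 = 3.5. The formula linking a score SD of 4.4 to the SD of change is therefore only a guide.

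Lastly, a separate analysis plan, not shown, may name the primary contrast. That would excuse silence. It does not cover a within-arm significance test that the article itself prescribes.

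**Conclusion.** The point holds as a fault in what section 2.10 prescribes: a within-arm test of continuous change at the same standard as the between-arm tests, not subordinated to them, and with no stated between-arm test of that change.

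Its size depends on assumed inputs. With no true effect, a 1-point gain shared by both arms and an SD of change of 2.5 to 4.4, the acupuncture-arm test is significant about 22% to 55% of the time at 29 per arm, and the discordant pattern appears up to about 25% of the time. A smaller gain lowers the first figure and a larger one raises it. The direction does not depend on the exact values: any shared gain lifts the within-arm rate above 5%. These are probabilities of a misleading within-arm statement, not of a false result from the planned between-arm tests. The point should be settled before analysis, but it does not undermine the design.

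**What to change.** In section 2.10, replace the before/after significance tests by a description: mean or median change in each arm with its 95% CI and no p-value. Treat the in-group Friedman test the same way.

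State that efficacy on MoCA, MMSE, UPDRSIII, NfL and GDNF is concluded only from the acupuncture-minus-sham comparison at week 5, with its 95% CI. Name the variable: either change from baseline, or the week-5 value adjusted for the baseline value already collected. Adjustment is the safer choice because it needs no more patients than a change score at any of the correlations checked.

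The cost is a few sentences of wording and the loss of the within-arm p-values. No patients, visits or measurements are added, and the planned 29 evaluable per arm is enough for either analysis at the correlations shown.

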##### Unified Parkinson’s disease rating scale motor examination (UPDRSIII)

2.6.2.2

The UPDRS is a commonly used scale for the overall evaluation of PD patients and consists of four parts. UPDRSIII mainly evaluates the motor function of the patients. There are 14 items in total, the highest score of each item is 4 points, and the total score is 56 points. The higher the score, the more serious the motor symptoms of PD patients.

The above scales will be assessed before and after treatment.

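### Section 2.10 names the Wilcoxon rank sum test, an independent-samples test, for paired before/after data; the signed-rank test is the counterpart (wrong as written, minor)

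*Protocol article*

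**What the plan says.** Section 2.10 of the protocol article sets the test by data structure and by the result of a Shapiro–Wilk normality check.

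- **Between groups:** an independent-samples t test if the data are normal with equal variances; otherwise "the Mann–Whitney U test will be used to compare the two groups with non-normal distribution".
- **Before versus after treatment:** the difference "before and after treatment will be treated by paired sample t test with normal distribution, and Wilcoxon rank sum test with abnormal distribution".
- **Repeated measurements that are not normal:** generalised estimating equations, and within a group "the simple effect in the group will be analyzed by Friedman test".

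The before/after data are paired. The UPDRSIII section closes its account of the three scales with "The above scales will be assessed before and after treatment". Table 2 schedules MoCA, MMSE, UPDRSIII, NfL and GDNF for the same patients at weeks 0 and 5.

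**The concern.** The two halves of the before/after sentence do not match. The normal branch is a paired test and uses the within-patient difference. The non-normal branch names a test that treats the week 0 and week 5 values as if they came from different people. That discards the pairing and uses the wrong variance for the comparison.

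The section also gives one procedure to two different data structures, because rank sum and Mann–Whitney U are the same test under two names. The test that fits the paired, non-normal case is missing.

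At stake is the consistency of the within-arm results. Followed literally, the plan would give endpoints that pass the normality check a correctly sized paired test. Endpoints that fail it would get a less sensitive one, and both would appear under the same significance threshold.

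**Working it through.** **1. Is the planned sample size affected?** Inputs from section 2.2: means 25.32 and 21.48, SDs 4.34 and 4.44, 90% power, 5% two-sided.

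- Difference: 25.32 − 21.48 = 3.84. Pooled SD: √[(4.34² + 4.44²)/2] = 4.39.
- Normal approximation: n = 2 × (1.960 + 1.282)² × 4.39² / 3.84² ≈ 27.5, so 28 per group.
- Noncentral t: power 0.895 at 28 and 0.905 at 29, so 29 per group, as stated.
- Dropout: 29/0.80 = 36.25 per group, close to the stated 36 (72 in total).

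This is a between-group calculation on independent samples. The before/after test does not enter it.

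**2. Direction of the error if the rank sum test were run on pairs.** With equal SDs σ and pre/post correlation ρ, the mean difference has variance 2σ²(1 − ρ)/n. An independent-samples test assumes 2σ²/n. For positive ρ the assumed variance is too large, so p-values are too large and the test is conservative. At ρ = 0 the two variances are equal.

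**3. Size of the error, whole-point scores.** Assumed inputs: 29 pairs (the evaluable number per group in section 2.2), SD 3, bivariate normal values rounded to whole points, two-sided 5%. The change tested is 1.22 points, the MoCA threshold in section 2.10. The article gives neither the pre/post correlation nor an SD of 3.

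| Correlation | Size: rank sum | Size: signed-rank | Power: rank sum | Power: signed-rank |
|---|---|---|---|---|
| 0.5 | about 1% | about 5% | about 25% | about 53% |
| 0.7 | about 0.2% | 4–5% | about 22% | about 76% |

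At correlation 0 the tests show no material difference. Repeat runs differ by one or two percentage points in power.

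**4. Same check on skewed data.** Assumed inputs: log-normal pairs, n = 29, a shift of 0.4 SD on the log scale, 4,000 replicates.

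| Correlation | Size: rank sum | Size: signed-rank | Power: rank sum | Power: signed-rank |
|---|---|---|---|---|
| 0 | 4.7% | 4.6% | 32% | 29% |
| 0.3 | 2.1% | 4.5% | 29% | 37% |
| 0.5 | 0.5% | 4.3% | 26% | 48% |
| 0.7 | 0.1% | 5.3% | 20% | 68% |
| 0.9 | 0.0% | 4.6% | 14% | 98% |

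The direction is the same in both settings. The rank sum test loses power as the correlation rises and does not produce extra false positives.

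**The case against.** The strongest reply is that this is a naming slip. Section 2.10 keeps paired and unpaired data apart elsewhere: it names Mann–Whitney U for the two groups and Friedman, a related-samples test, within groups. Where it needs a partner for the paired t test it uses a different name, Wilcoxon, so signed-rank may well have been intended. That is plausible and perhaps the likelier reading, but the text does not settle it, and an analyst following it literally would run the wrong test.

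A second reply concerns the figures. SD 3 and the correlations are assumptions; section 2.2 gives SDs of 4.34 and 4.44 for MoCA. Rounded normal data would also mostly pass the normality check and go to the paired t test. In a check with an assumed mean of 21.5, Shapiro–Wilk rejected the differences in about 9–10% of data sets at correlation 0.5 and about 15% at 0.7. Both remarks stand. The first table therefore illustrates how the two tests differ and does not predict this trial's results. The log-normal check, which suits the non-normal branch better, points the same way. How often that branch would be used is unknown, because the article gives no distributional shape for any endpoint.

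A third reply is that only within-arm comparisons are touched. That is correct and limits the severity. A reader might infer that the trial means to claim efficacy from within-arm tests. The article does not say so: it specifies between-group tests and a between-group comparison of responders.

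**Conclusion.** Wrong as written, and minor. Section 2.10 names an independent-samples test for paired data, and the matching paired test appears nowhere in the article.

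The consequence depends on two conditions: that the rank sum test is actually run, and that pre- and post-treatment values correlate positively, as repeated values in the same patient would be expected to do. Under the assumed inputs, power would then fall by about half at correlation 0.5 (53% to 25%) and by more at 0.7 (76% to 22%), with size well below the nominal 5%.

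A reader might infer that every non-normal before/after p-value will be wrong, or that false positives will rise. The documents do not support either reading. The wording may be a slip, the two tests agree when the correlation is zero, and with positive correlation the error is towards conservatism. The randomised comparison by t test or Mann–Whitney U, the MoCA responder chi-square test and the sample size of 72 are unaffected.

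**What to change.** In section 2.10, replace *Wilcoxon rank sum test* with *Wilcoxon signed-rank test* for before/after comparisons, and leave Mann–Whitney U for the between-group comparison. The same edit serves whether the wording is a slip or was intended. It changes one test name and needs no new data, no change to the sample size and no change for patients.
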